## Abstract

**Background:**

India records the highest number of suicide deaths globally, but suicide prevention efforts are hindered by a lack of trained personnel within the public health system. Given that an index suicide attempt is a strong predictor of future suicide, intervening with individuals who have recently attempted suicide is a targeted prevention approach that can be delivered within the public health system and has potential to be scaled up across low-resource settings.

**Aim:**

To test the implementation and preliminary effectiveness of Contact and Safety Planning (CASP) in reducing suicidal behaviour and symptoms of depression among adults with a recent suicide attempt in Chhattisgarh.

**Methods:**

We will carry out a non-randomized, controlled pilot study to evaluate the feasibility, acceptability, adoption, reach, implementation (including cost) and preliminary effectiveness of CASP when delivered by health workers – emergency nurses and Community Health Officers – in two districts of Chhattisgarh (n=250). The control group will receive Enhanced Usual Care, consisting of telephonic counselling by trained District Mental Health (n=250) program staff. Data will be collected at baseline and at 6-
and 12-month follow- up.

**Conclusion:**

This study will shed light on the feasibility of CASP and inform its further refinement to address suicide at scale in India.

**Trial Registration:**

Clinical Trials Registry India (CTRI/2022/12/048087) dated 1 October 2022.
Link here.

List of abbreviationsBICBrief Intervention and ContactCASPContact and Safety PlanningCHCCommunity Health CenterCHOCommunity Health OfficerCSSRSColumbia Suicide Severity Rating ScaleDMHPDistrict Mental Health PlanEUCEnhanced Usual CareEQ-5D-5LEuroQol-5D-5LHWCHealth and Wellness CenterNCRBNational Crime Records BureauPHCPrimary Health CentrePHQ-9Patient Health Questionnaire-9RMARural Medical AssistantSCScheduled CasteTiC-P
Treatment Inventory of Costs in PatientsWHOWorld Health Organisation

## Introduction

Suicide is a leading threat to the well-being of communities globally, and particularly in India which reports the highest number of suicide deaths in the world.
^
1
^ Although Indians make up 18% of the world’s population, India accounts for 26.6% of suicides globally.
^
2
^ Since 2017, suicide rates in India have increased steadily with suicide ranking as the first and second leading cause of death among young women and men aged 18-39 respectively.
^
3,
4
^ Data from the National Crime Records Bureau (NCRB) indicates an upward trajectory, with a national suicide rate of 12.4 per 100,000 individuals in 2022 up from 12 in 2021, marking the highest rate in NCRB history.
^
4
^ This is despite a recognized under-reporting of suicides in India by as much as 30-100%.
^
3,
5
^

Chhattisgarh, a central Indian state, has a suicide rate of 28.2 per 100,000 (2022), the fourth highest among states in India and more than double the national suicide rate of 12.4 per 100,000.
^
4
^ The Chhattisgarh District Mental Health Program (DMHP) was designed to offer telephonic and in-person follow-up counselling for individuals who have attempted suicide; however, most DMHP clinics are unable to implement the intended program due to a dearth of specialized providers, such as psychiatrists, psychologists or counsellors trained to respond to suicide. Consequently, in many districts, there is no follow-up by a professional after a suicide attempt, despite prior research demonstrating that a previous suicide attempt is one of the strongest predictors of future attempts.
^
6,
7
^

Although the State Government of Chhattisgarh is drafting a State Suicide Prevention Strategy (not yet published); the lack of human resources is a significant constraint in the state which necessitates the mobilization of public health resources to implement suicide response and prevention measures. Contact and Safety Planning (CASP) is an adaptation of brief intervention and contact (BIC) and safety planning interventions, methods which have been effective in reducing suicidal behavior among high-risk individuals worldwide.
^
7–
10
^ CASP was developed and adapted from evidence-based safety interventions for the Indian context by SNEHA, Chennai and showed to be effective, feasible and acceptable when delivered among a refugee population in Tamil Nadu.
^
8
^ BIC has been effective in reducing repeat suicides in a 5-country study
^
11,
12
^ and is recommended by the World Health Organisation (WHO) as an effective intervention to reduce suicides and attempted suicides in the general population.
^
13
^ Safety planning interventions have been found to reduce fatal and non-fatal suicide attempts in a recent meta- analysis
^
9
^ and when tested in conjunction with brief contact among veterans in the US.
^
14
^ Leveraging the public health system to deliver CASP may be a promising solution to address the treatment gap for suicide in Chhattisgarh and similarly low-resourced settings, however, the feasibility and acceptability of a health-systems approach for CASP is yet to be determined.

This study will integrate CASP into the public health system by training non-specialist health workers to identify and follow up with adults who have recently attempted suicide in two districts where the DMHP is not providing any response to suicide attempts (due to personnel shortages). We will train two groups of health workers: (1) nurses in emergency wards of health centres to identify and recruit adults who have attempted suicide from emergency wards, and (2) Community Health Officers (CHOs) at community-based Health and Wellness Centers (HWCs) to deliver the CASP intervention in the community over an 11-week follow-up period.

Follow ups by CHOs will include suicide risk assessments, provision of emotional support and empathetic listening, and collaborative safety planning to identify steps a participant can follow if they are in distress. Steps include identifying symptoms of distress, recognizing coping mechanisms and planning for future use of coping strategies, activating support networks, referrals for professional care and sharing details of the nearest emergency services. The first follow up visit will occur within one week of discharge from a healthcare facility post-attempt, and then continue periodically over the immediate 11-week period afterward.

## Protocol

### Aims

The primary aims of this study are to assess the feasibility, acceptability, reach, adoption and implementation (including cost) of delivering the CASP intervention within the public health system in Chhattisgarh.

The secondary aim is to assess:
•Difference in rate of suicide re-attempt at 6 and 12 month follow up between intervention and control groups,•Preliminary impact on suicidal behaviour and symptoms of depression at 6 and 12 month follow up within the intervention group only.

For the purposes of this study, suicidal behaviour is defined as inclusive of suicidal intention, ideation, planning and fatal or non-fatal suicide attempt.

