### Participants

We will recruit adults (≥18 years of age), who present to emergency public health facilities (district hospitals, primary or community health centers) in Balod and Rajnandgaon districts with attempted suicide or are already admitted for attempted suicide within one week of the study start date. We will exclude individuals who are unable to communicate clearly due to medical conditions or speech/hearing disabilities despite reasonable accommodations, those unable to comprehend one of the local languages used by CHOs to deliver the intervention, and individuals who do not reside within the catchment area of Balod and Rajnandgaon Health and Wellness Centers (where trained CHOs are placed).

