### Recruitment & Retention

Individuals presenting at district hospitals, Primary Health Centres (PHCs), or Community Health Centres (CHCs) following a suicide attempt will be identified by casualty nurses, who will screen for eligibility and invite those meeting the criteria to participate in the study. After providing a brief explanation of the study, the nurses will obtain verbal consent from interested individuals and notify the research team via telephone, sharing details such as the participant’s village of residence and hospital discharge date.

The research team will then assign a Community Health Officer (CHO) from the nearest Health and Wellness Center to follow up with the participant at a time and place of their convenience. Within one week of discharge, the CHO will meet the participant, obtain written informed consent, and initiate follow-up care as per the CASP intervention protocol.

During the informed consent process, the CHO will explain the study’s purpose, procedures, and the potential risks and benefits of participation, emphasizing that involvement is entirely voluntary. Participants will receive a consent form and an information sheet detailing the study objectives, procedures, and the contact information of CASP research team members, enabling them to seek clarifications or address concerns at any point during the study.

To support participant retention in the study, we will make up to five contact attempts over a two-week period following each scheduled follow-up appointment. These attempts will include a combination of telephone calls and in-person home visits (where feasible and safe).

If a participant misses a follow-up but can be contacted later, they will still be approached for subsequent follow-ups at later time points.

For participants who actively request to discontinue follow-ups, the study team will first explore and address any concerns to encourage continued participation. However, if the participant continues to decline, they will be formally withdrawn from the intervention and no further contact will be made.

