### Data collection

Baseline demographic data—including age, gender, education, marital status, employment status, caste/tribal background, income, and contact details—will be collected by Community Health Officers (CHOs) from consenting participants. Study records will include the following: (1) record books maintained by nurses at health facilities, documenting the date, age, gender, method of attempt, verbal consent status, and, if applicable, reasons for refusal; and (2) CHO records detailing the dates and locations of participant visits to monitor adherence to the CASP intervention schedule (at 1, 2, 4, 7, and 11 weeks post-attempt).

For outcome assessments, the Columbia-Suicide Severity Rating Scale (C-SSRS) and the Patient Health Questionnaire-9 (PHQ-9) will be administered to participants in the intervention group at baseline and during follow-ups at 6 and 12 months. Within the control arm, a brief follow up survey will be administered that captures suicide re-attempt at 6 and 12 month follow up points. Data collection will be conducted by trained data collectors, who are local Master’s graduates in mental health or related fields with prior experience in the health system.

To support the cost analysis and economic evaluation, a brief cost survey (Modified TiC-P) and the EuroQol-5D-5L will be administered to a random sample of 50 participants in both the intervention and control groups at baseline and at the 6-month follow-up. Data collection will be conducted using paper-and-pencil assessments or self-administered forms, based on participant preference.

Qualitative follow-up data will be collected through in-depth and semi-structured interviews, lasting approximately one hour each. These interviews will be conducted by research team members and audio recorded with prior informed consent for transcription purposes. Acceptability interviews with participants will include a random sample selected independently of intervention completion status, ensuring the inclusion of individuals who may have dropped out of the study. See
Figure 1 for research and data collection procedures.

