### Data analysis

*Implementation outcomes*

Descriptive statistics (means, medians and standard deviations) of the reach, adoption and implementation metrics will be calculated. Qualitative thematic analysis
^
27
^ of the in-depth interviews exploring feasibility and acceptability will be carried out using a mix of inductive and deductive approaches. Two coders will independently review transcripts, generate initial codes, and collaboratively develop a comprehensive codebook (initial coding). This will be followed by a pilot coding phase to ensure procedural consistency before independent coding of the remaining transcripts, with discrepancies resolved through consensus or third-rater consultation. Researchers will then interpret and refine final themes. Coding will be done using NVivo 1.4.1.

*Clinical outcomes*
1.Difference in percentage of re-attempted suicide and death by suicide

We will analyze the difference between the intervention and control group in the percentage of participants who, after initial visit in the hospital for a suicide attempt, have re-attempted suicide (including deaths by suicide) at 6 and 12 months of follow-up. For statistical analysis, we will use Bayesian binominal testing as implemented in the open software program JASP.
^
28
^ Bayesian analysis allows us to not only test whether the null hypothesis is true or false, but also to test how likely the alternative hypothesis (that the change in suicide rates between intervention and control) is given the data.
^
29,
30
^
2.Change in depression, suicide risk and TiC-P scores

The mean change in depression and suicidal behavior scores between baseline and 6-
and 12-
months follow-up within the intervention group will be calculated using Bayesian linear mixed models as implemented in JASP. Models will be estimated both with and without a random effect for location, to see if it is needed to control for any clustering effect.
^
31
^
3.Quality of life

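### The depression result is labelled preliminary effectiveness and impact of CASP, but the PHQ-9 is collected and analysed only within the CASP arm, so change cannot be attributed to CASP

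*Protocol article*

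**What the plan says.** For people who have lately attempted suicide, the abstract states its aim as "To test the implementation and preliminary effectiveness of Contact and Safety Planning (CASP) in reducing suicidal behaviour and symptoms of depression". The Aims section separates two clinical questions. Re-attempt is compared between arms. The other is "Preliminary impact on suicidal behaviour and symptoms of depression at 6 and 12 month follow up within the intervention group only".

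Data collection follows that split. The C-SSRS and PHQ-9 "will be administered to participants in the intervention group at baseline and during follow-ups at 6 and 12 months". For controls the text reads: "Within the control arm, a brief follow up survey will be administered that captures suicide re-attempt at 6 and 12 month follow up points". Under Data analysis (Clinical outcomes), mean changes in depression and suicidal behaviour scores from baseline to 6 and 12 "months follow-up within the intervention group will be calculated using Bayesian linear mixed models as implemented in JASP". No external benchmark for PHQ-9 change is given, natural recovery and regression to the mean are not mentioned, and the change is not labelled descriptive.

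On entry, the Participants section takes adults who come to public emergency facilities "with attempted suicide or are already admitted for attempted suicide within one week of the study start date". Recruitment & Retention adds: "Within one week of discharge, the CHO will meet the participant, obtain written informed consent, and initiate follow-up care".

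**The concern.** *Effectiveness* and *impact* are causal words: they claim that depressive symptoms fell because of CASP. A before–after change in one arm combines any CASP effect with whatever would have happened anyway. In people enrolled because of a recent crisis, the second part is unlikely to be nil. Distress is plausibly high soon after an attempt and may ease over 6 to 12 months through recovery and regression to the mean.

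An analysis plan could not repair this, because the comparison data are not collected. At stake is how the depression finding is reported. The protocol plans a policy brief of key findings, and the Discussion promises early indications of effectiveness. A reader of the abstract alone would not learn that the depression result has no comparator.

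**Working it through.** **1. Do the sections leave any comparator for depression?**
- Abstract, Aim: preliminary effectiveness on depressive symptoms; no mention that this is single-arm.
- Aims: preliminary impact, intervention group only.
- Data collection: PHQ-9 in the CASP arm only; controls get a re-attempt survey.
- Data analysis: change from baseline in the CASP arm only.

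The last three agree with one another, so this is a deliberate design choice. The plan yields one quantity, mean PHQ-9 change under CASP, and none for change under Enhanced Usual Care.

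**2. Is there a figure in the plan to reproduce?** Not for this outcome. The sample size of 250 per arm is set for re-attempt. No effect size, SD or threshold is stated for PHQ-9 change. The calculation below is therefore an illustration, not a property of a rule in the protocol.

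**3. Illustration in SD units.**

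Inputs:
- n = 250 × (1 − 0.20) = 200 analysed (Sample size section).
- True CASP effect = 0.
- d = natural fall in PHQ-9 SD units (assumed).
- r = correlation of baseline with follow-up, 0.3 to 0.5 (assumed), with equal SDs at both times.
- Supposed rule: a two-sided 95% interval for mean change that excludes zero on the favourable side is read as an effect.

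The SD of change, in PHQ-9 SD units, is √(2(1 − r)): 1.183 for r = 0.3 and 1.000 for r = 0.5.

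Chance of a favourable reading = Φ( d√200 / √(2(1 − r)) − 1.96 ).

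Example, d = 0.2: 0.2 × 14.142 = 2.828. For r = 0.3, 2.828/1.183 − 1.96 = 0.43, giving 0.667. For r = 0.5, 2.828 − 1.96 = 0.87, giving 0.807.

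| Assumed natural fall | r = 0.3 | r = 0.5 |
|---|---|---|
| 0.1 SD | 22% | 29% |
| 0.2 SD | 67% | 81% |
| 0.3 SD | 95% | 99% |

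**4. The same in PHQ-9 points**, with an assumed SD of change of 5 to 8. The interval excludes zero once the observed mean fall exceeds 1.96 × SD/√200, which is 0.69 points (SD 5) to 1.11 points (SD 8). The chance of a favourable reading with no CASP effect is 81% to 42% for a natural fall of 1 point, 99% to 76% for 1.5 points, and over 99% to 94% for 2 points.

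**5. A Bayesian proxy**, since the planned models are Bayesian. With a default one-sample Bayes factor (Cauchy scale 0.707) above 3 as the supposed rule, the chance is 54% to 17% for 1 point and over 99% to 79% for 2 points, over the same SD range.

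Steps 3 to 5 ignore clustering by location. Allowing for it would widen the intervals and lower these chances.

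**6. What a control PHQ-9 would give.** At 200 per arm, the between-arm difference detectable with 80% power is (1.96 + 0.84) × SD × √(2/200): 1.4, 1.7 and 2.0 points for an assumed SD of change of 5, 6 and 7. A fall common to both arms would cancel; differences between districts would not.

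**The case against.** The strongest reply is that the protocol is open about most of this. Both causal words carry the qualifier *preliminary*, the aim itself says intervention group only, and the analysis section already describes within-group change. This is a pilot whose primary aims concern implementation. That stands as a limit on seriousness. It does not answer the point, because *preliminary* speaks to precision and does not supply a comparator.

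A reader might go further and infer that a positive depression result is likely even if CASP does nothing, and that it would feed the decision on a definitive trial. The documents do not support this:
- No test against zero, interval rule or Bayes-factor cut-off is stated for PHQ-9 change.
- The natural fall and the correlation are not in the documents. At 0.1 SD a favourable reading is the less probable outcome.
- The date of the baseline PHQ-9 is not stated. The one-week window is for consent and first contact by the Community Health Officer (CHO), so an early baseline is an inference.
- Table 2 rests progression on recruitment, retention, CHO continuation and qualitative findings. The PHQ-9 has no part in it.
- The Dissemination section does not name depression among the findings for the policy brief.

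It can also be said that a control PHQ-9 would be confounded. The arms are not randomized, and the control districts have an active DMHP and monthly awareness camps that the intervention districts lack. That stands, and is why such a comparison could only be exploratory. EQ-5D-5L, with its anxiety/depression dimension, is taken in both arms at baseline and 6 months, but in only 50 per arm. It does not replace the PHQ-9.

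**Conclusion.** The point holds as a mismatch between claim and design. Followed exactly, the plan measures change in depressive symptoms among CASP participants and cannot attribute that change to CASP, so *effectiveness* and *impact* are not supported for this outcome. This conclusion rests on the text alone and needs no assumed number.

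The size of the problem does depend on assumptions. Under the illustrative interval rule the chance of a favourable reading without any CASP effect runs from 22% at a natural fall of 0.1 SD to 99% at 0.3 SD. This shows that attribution is unsafe; it does not establish that a false positive is likely. Consequences are limited because depression is secondary and outside the progression criteria. The re-attempt comparison has a control arm and is not touched by this point.

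**What to change.** **Lead change, possible at any stage.** In the abstract's Aim and in the Aims section, replace *effectiveness* and *impact* for depression with *uncontrolled change in PHQ-9 among CASP participants*. With the analysis of depression scores, state that this change is descriptive and is not evidence of a CASP effect.

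**Where control contacts still remain.** Add the PHQ-9 to the control consent contact, which data collectors already make (Ethics and consent), and to the existing 6- and 12-month control survey. Report a between-arm difference adjusted for baseline PHQ-9 in those with a baseline value. Label it exploratory, because the arms are not randomized and the districts differ in DMHP services.

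This second part may reach few people. Recruitment and follow-up are under way and data collection ends in November 2025. A full 12-month follow-up by then implies enrolment by about November 2024, so most control baselines are probably beyond recovery.

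**Cost.** A weaker depression claim, a few minutes per remaining control contact, and an amendment notified to the two ethics boards and the registry as the Protocol amendments section requires.

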### Study design

The CASP intervention will be tested in the form of a 1:1 non-randomized, controlled pilot study. The pilot study will consist of two arms, comparing the CASP intervention in the two districts of Balod and Rajnandgaon against Enhanced Usual Care in the two districts of Mungeli and Balodabazar.

### Setting

The Central Indian state of Chhattisgarh, formerly a part of Madhya Pradesh, was granted statehood in 2000 and is the ninth largest state in India (estimated population 25.5 million).
^
15
^
^,^
^
16
^ 75% of the population live in rural areas and the state has the highest tribal population among large states in India with one-third of its population belonging to tribal communities.
^
16,
17
^ Chhattisgarh is divided into 32 districts as of 2021, 28 of which are covered by the Government’s District Mental Health Program (DMHP).
^
18
^ In 2022, Chhattisgarh contributed 4.9% of India’s suicide burden, with a rate of 28.2 per 100,000 people, more than twice the national average (12.0).
^
4
^ According to the National Mental Health Survey (2016), approximately 0.28% of the population in Chhattisgarh is at high risk of suicide, with the highest risk group being 18–29-year-olds.
^
15
^ As per the NCRB, factors which contribute to suicide in Chhattisgarh include financial difficulties among men such as bankruptcy or indebtedness, and marriage related problems among both men and women.
^
4
^ The mental health treatment gap is also high in Chhattisgarh, ranging from 54.5 % (for psychosis) to 80.1% (for common mental disorders).
^
19
^

*Intervention district selection*
^
16
^

Rajnandgaon is home to an estimated 1.8 million people, with 82.27% residing in rural areas. The population includes 26% Scheduled Tribe (ST) and 10% Scheduled Caste (SC) communities and shows a 52% work participation rate. As a larger district, Rajnandgaon consists of 6.02% of the state’s population. It comprises 9 blocks with 1 district hospital, 1 medical college, 10 community health centres, and 47 primary health centres.

Balod district is home to approximately 0.8 million people, with 88% living in rural areas. 31% of the population belong to ST communities, and 8% to SC communities. The district’s work participation rate is 51%, and it is divided into 5 blocks and 704 villages. The healthcare infrastructure includes 1 district hospital, 5 community health centres, and 30 primary health centres.

Both districts lack follow-up care for attempted suicide cases in healthcare facilities, a gap this study aims to address by training health workers placed at multiple levels of the health system in these districts.

*Control district selection*

Balodabazar and Mungeli are two predominantly rural districts in Chhattisgarh. Balodabazar has a total population of approximately 1.31 million, with 87.25% residing in rural areas. The district’s population includes 23.37% Scheduled Castes (SC) and 12.8% Scheduled Tribes (ST). The district is administratively divided into six blocks and is served by one district hospital, six community health centres (CHCs), and 31 primary health centres (PHCs).

Mungeli has a smaller population of approximately 0.70 million, with an even higher rural proportion (90.67%). Its population comprises 27.76% SC and 10.37% ST. Mungeli consists of three blocks and is served by one district hospital, three CHCs, and 28 PHCs.

Like Balod and Rajnandgaon, Balodabazar and Mungeli are characterized by a predominantly rural, socially disadvantaged population and limited health infrastructure.

